# Comparison of BARD®LIFESTREAM™ covered balloon-expandable stent versus GORE® VIABAHN™ covered self-expandable stent in treatment of aortoiliac obstructive disease: study protocol for a prospective randomized controlled trial (NEONATAL trial)

**DOI:** 10.1186/s13063-022-06332-7

**Published:** 2022-05-12

**Keywords:** Randomized controlled trial, Covered balloon-expandable stent, Covered self-expanding stent, Aortoiliac obstructive disease

## Abstract

**Background:**

Covered stent has become one of the mainstream therapies for aortoiliac obstructive disease (AIOD), with a higher patency rate than bare metal stent. Covered balloon-expandable (CBE) stent can be placed more accurately with higher a radial support force, while covered self-expanding (CSE) stent has greater elasticity and higher trackability. However, there is no level I evidence regarding the comparison safety and efficacy between the CSE stent and CBE stent in AIOD to date. Therefore, this study aims to compare the efficacy and safety of CBE stent (BARD®LIFESTREAM™) and CSE stent (GORE® VIABAHN™) in AIOD.

**Methods:**

This trial is a prospective, single-center, parallel, noninferiority, randomized controlled trial. A total of 106 patients will be enrolled and these patients will be randomized to either the CBE stent group or the CSE stent group. The primary end point of the study is the occurrence of target lesion revascularization (TLR) at 12 months after the intervention.

**Discussion:**

To our knowledge, the ballooN sElf cOver steNt AorToiliAc occuLusive (NEONATAL) trial is the first RCT to compare CBE and CSE stent in AIOD patients. The main aim is to compare the TLR of the target lesion between CBE stent and CSE stent at 12 months post-procedure. The results of clinical trials may contribute to establishing a strategic guideline for choosing the optimal type of covered stent in the treatment of AIOD patients.

**Trial registration:**

Chinese Clinical Trials Registry ChiCTR2100046734. Registered on 27 May 2021

**Supplementary Information:**

The online version contains supplementary material available at 10.1186/s13063-022-06332-7.

## Introduction

Aortoiliac obstructive disease (AIOD) is a common chronic atherosclerotic arterial occlusive disease involving infrarenal aorta or iliac arteries that accounts for approximately one-third of all peripheral artery disease cases and places a high economic burden on treatment [1]. Trans-Atlantic Inter-Society Consensus (TASC) recommends the endovascular approach as the preferred treatment for TASCII A and B aortoiliac lesions instead of open surgery [2]. A related systematic review showed that endovascular treatment was considered valid as open surgical revascularization due to shorter hospitalization and a similar long-term patency rate in TASCII C and D lesions [3, 4]. Furthermore, the recent guideline from the European Society of Vascular Surgery suggested that an endovascular-first strategy may be considered for aorto-iliac occlusive lesions if performed by an experienced team [5]. Regarding device selection in aortoiliac artery interventions, covered stents have a higher class of recommendation in moderate to severe calcified and diffuse lesions than bare metal stents with superior patency rate [6–8].

Covered stents are classified as self-expandable or balloon-expandable, according to the mechanics of stent deployment. Technically, self-expandable stents have greater elasticity, allowing them to maintain their shape after post-dilation and continue to expand as the vessel remodels until they reach the appropriate size. In addition, self-expandable stents are more flexible and trackable; thus, they more easily pass through tortuous vessels. By comparison, balloon-expandable stents have much greater radial support strength, which is especially vital in diffuse, heavily calcified lesions. In addition, balloon-expandable stents can be deployed more precisely with minimal geographic displacement; hence, they are adopted widely in lesions involving aortic bifurcations.

Current evidence has shown that the 1-year restenosis rate and target lesion revascularization rate of self-expandable bare stents are higher than those of balloon-expandable bare stents in AIOD patients [9]. However, the efficacy and safety of covered balloon-expandable (CBE) stents versus covered self-expanding (CSE) stents in the treatment of aortoiliac obstructive disease remain unknown.

Current evidence regarding CBE and CSE stents in AIOD mainly focuses on comparisons with bare metal stents (BMSs). Several studies suggested that patients who received CBE stents had an enduring patency advantage, a lower rate of revascularization, and a similar limb amputation rate compared with those who received BMS [6, 8]. Additionally, another study showed that CBE stents were superior to bare metal balloon-expandable stents for the treatment of common iliac artery (CIA) disease at 3 years regarding primary patency, assisted patency, and secondary patency [10]. However, another study demonstrated that the use of CSE stents has similar early and midterm outcomes compared with BMS in severe iliac lesions, while CSE seemed to have higher midterm patency than BMS only in TASC D subjects [11]. As there is no direct comparison between CSE and CBE stent in AIOD patients, no definitive conclusion can be drawn regarding which type of stent is superior.

The Gore Viabahn endoprosthesis (W. L. Gore and Associates, Flagstaff, Ariz) and LifeStream covered iliac stent (Bard Peripheral Vascular, Inc, Tempe, Ariz) represent one of the most widely used CSE and CBE stents, respectively. This prospective, single-center, parallel, noninferiority, randomized controlled trial aims to compare the safety and efficacy of CSE stents and CBE stents in AIOD patients, with a special focus on midterm and long-term freedom from target lesion revascularization (TLR).

## Methods/design

### Ethics and dissemination

This study was approved by the Ethics Committee on Biomedical Research, West China Hospital of Sichuan University (approval number: 2021-212) on 11 March 2021. The trial was registered in the Chinese Clinical Trial Registry (registration number: ChiCTR2100046734) on 27 May 2021.

### Protocol amendments

In our trial, simple size may be adjusted based on TLR at 12 months post-procedures, which will be notified to the Ethics Committee on Biomedical Research, monitoring committee, and the upstream authorities. Other non-substantial amendments will not be notified to the monitoring committee and the upstream authorities, but will be recorded by researcher. Update informed consent forms will be sent to new patients after amendments, and all researches will be informed correspondently.

### Data access

Project principal investigators, ethics committee, and monitoring committee will have access to the final trial dataset and all data information will be de-identified. Furthermore, independent institution will be contacted for monitoring and quality assurance during the conduct of the study.

### Post-trial care

There is no underlying harm for trial participant when LIFESTREAM or VIABAHN stent placed. After the procedure, patients will be provided with guidance on specialized treatment protocols and dressing changes.

### Study setting

The NEONATAL trial is a prospective, single-center, parallel, noninferiority, single-blind, randomized controlled trial (allocation ratio 1:1), planned to be conducted in West China Hospital, Chengdu, China. The present protocol was written according to the Standard Protocol Items: Recommendations for Interventional Trials (SPIRIT) 2013 Statement for study protocols of clinical trials [12]. Patient-centered care was involved in the design of our protocol. We conducted a preliminary survey in patients to investigate the outcomes they care most and the follow-up methods that they prefer. The SPIRIT flow diagram is shown in Fig. 1, and the SPIRIT Checklist is added in Additional file 1. Table 1 shows the schedule of enrollment, interventions, and assessments.

**Fig. 1 Fig1:**
[figure not shown]
The procedure of screening, randomization, and follow-up of patients in the trial

**Table 1 Tab1:**
[figure not shown]
The schedule of enrollment, interventions, and assessments

### Eligibility criteria

Patients at least 18 years old who are diagnosed with AIOD (Rutherford classification from 2 to 6) will be screened for study recruitment. The inclusion and exclusion criteria are shown in Table 2.

**Table 2 Tab2:** Inclusion criteria and exclusion criteria

Inclusion criteria	Exclusion criteria
The participants meeting the following criteria will be included: (1) The subject is a male or non-pregnant (or no plan to become pregnant during study) female ≥ 18 years old with an expected lifespan sufficient to allow for completion of all study procedures. (2) Symptomatic peripheral artery disease with moderate to severe claudication (Rutherford score of 2 to 3); chronic CLI with resting ischemic pain (Rutherford score of 4); chronic CLI with ischemic ulcers (Rutherford score of 5 to 6). (3) Subjects diagnosed with aortoiliac obstructive disease (Trans-Atlantic Inter-Society Consensus, TASC II, TASC II A-D). (4) The target lesion(s) can be successfully crossed with a guide wire and pre-dilated with an appropriately sized percutaneous endovascular angioplasty (PTA) balloon. (5) The subject provides informed consent using an informed consent form (ICF) that is reviewed and approved by the Ethics Committee (EC).	The participants meeting the following criteria will be excluded: (1) The subject is asymptomatic, has mild claudication described as Rutherford Category 0 (asymptomatic) or 1 (mild claudication). (2) The subject has a vascular graft previously implanted in the native iliac vessel. (3) The subject has an abdominal aortic aneurysm (AAA) contiguous to the iliac artery target lesion(s) or subject has a pre-existing target iliac artery aneurysm or perforation or dissection of the target iliac artery. (4) The subject has a serum creatinine ≥ 2.5 mg/dl or is currently on dialysis. (5) The subject has a known uncorrectable bleeding diathesis or active coagulopathy (platelet count< 80,000/μL). (6) The subject has intolerance to the antiplatelet, anticoagulant, or thrombolytic medications. (7) The subject has a known allergy or sensitivity to stainless steel (i.e., Nickel), ePTFE or contrast media. (8) The subject suffered a stroke, or transient ischemic attack (TIA) within 3 months prior to the procedure.

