### Allocation and implementation of interventions

Prior to the endovascular intervention, patients will be enrolled, and informed consent will be obtained from all participants by surgeons. The included patients were randomly allocated at a 1:1 ratio to the CBE stenting group or the CSE stenting group using Statistical Analysis System (SAS, version 9.4) by a biostatistician within sex and 5-year age groups in blocks of ten, and stratification was performed by numbers of treatable legs. For patients who required intervention in bilateral iliac arteries, randomization was performed according to the treated arteries. The sealed, opaque, consecutively numbered envelopes were used to keep the allocation code for each participant, which will be kept unopened by an independent research assistant. The nurse research coordinator in the operating room will prepare the envelopes and inform the surgeon of the allocation results before intervention. Both nurse research coordinators and biostatisticians were not involved in the perioperative management of patients. The outcome assessors and data analysts will be blinded to the interventions.

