### Details of intervention

The included patients will receive the same perioperative management, including antiplatelet drugs, statin usage, and blood controls. Both common femoral arteries and sometimes brachial artery will be used for access. Whether to adopt percutaneous or cutdown access route will be determined by the surgeons. After obtaining arterial access, 0.5 mg/kg of unfractionated heparin will be administered. A fluor opaque ruler will be used to record the location and extent of the lesion. Both intraluminal and subintimal recanalization of iliac lesions will be allowed. After the successful passage of the guidewire, the target lesion will be predilated with downsized balloon in CBE group, and with equal-sized balloon in CSE group. During actual intervention, the allocated choice of covered stents may be modified according to intraoperative findings, for instance, the length of lesions did not match the stents. Multiple stents are required when needed and multiple stent edges should overlap by at least 10 mm. Furthermore, additional bare metal stents can be added in both groups, according the discretion of surgeons. Post-dilation balloon will be performed within the stented segment, with less than 10% oversizing. Final angiography will be performed after the intervention in both groups, with the same angles and magnifications as the baseline angiography.

Postoperative management include a dual antiplatelet regimen for 3 months, involving 100 mg of aspirin once a day plus 75 mg of clopidogrel once a day. Clopidogrel is not required if a participant is taking warfarin; other direct thrombin inhibitors, factor Xa inhibitors, or low molecular weight heparin will be used according to the physician’s recommendation. Anticoagulant therapy will be discontinued when other surgical procedures are needed, and then, the participant will resume anticoagulant therapy as soon as possible after the surgery. Drug side effects will be checked and monitored at outpatient visit or telephone follow-up. According to the comprehensive surgeon’s recommendation, drug therapy will be discontinued. Clinical follow-up will be planned at 1, 6, 12, 24, and 36 months to evaluate clinical outcomes.

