### Statistical analysis

R studio Version 1.2.1335 (http://www.R-project.org) and Empower (www.empowerstats.com, X&Y solutions, Inc., Boston, MA) were utilized for statistical analysis. Categorical data are expressed as numbers and rates, while continuous data are expressed as means ± standard deviation (SD) if they are normally distributed, or median (interquartile range [IQR]) vice versa. Student’s *t* test or Mann-Whitney *U* test is used for univariate analysis of continuous data, and the *χ*^2^ test or Fisher’s exact test is used for categorical data. For primary analyses, multivariate logistic regression is adopted to calculate adjusted odds ratios (ORs) and 95% confidence interval (95% CI) for short-term outcomes. Cox proportional hazard regression analysis is used to generate adjusted hazard ratio (HR) and corresponding 95% CI for long-term outcomes. The primary and secondary end points will be analyzed in the modified intention-to-treat analysis, which includes all subjects undergo randomization and subsequent interventions. Sensitivity analyses of primary and secondary endpoints are performed in the per-protocol population, based on the treatment actually received. The noninferiority margin was set at 10 percentage points for the absolute difference between groups. If the standard of noninferiority was reached, the primary and secondary outcomes were subsequently tested for superiority (*P*<0.05). Noninferiority will be considered proven if conclusions drawn from the intention-to-treat and per protocol analyses are consistent.

Further pre-specified subgroup analyses will be carried out in the following subgroups: TASC II C-D lesions versus A-B lesions, occlusion versus stenosis. Adjustment analyses for primary and secondary endpoints were performed based on the Hochberg method [16]. Multiple imputation was used to handle missing data.

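### At least the pre-dilation part of inclusion criterion 4 is judged after the surgeon knows the arm, so exclusions and stent switches can differ between arms

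*Protocol article*

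**What the plan says.** All references are to the protocol article.

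- **Eligibility criteria, Table 2, inclusion criterion 4:** "The target lesion(s) can be successfully crossed with a guide wire and pre-dilated with an appropriately sized percutaneous endovascular angioplasty (PTA) balloon".
- **Allocation and implementation of interventions:** "Prior to the endovascular intervention, patients will be enrolled, and informed consent will be obtained from all participants by surgeons". In the operating room the nurse coordinator will "inform the surgeon of the allocation results before intervention". Outcome assessors and data analysts are blinded; the surgeon is not.
- **Details of intervention:** after arterial access, "A fluor opaque ruler will be used to record the location and extent of the lesion". Once the wire has passed, "the target lesion will be predilated with downsized balloon in CBE group, and with equal-sized balloon in CSE group". Then, "the allocated choice of covered stents may be modified according to intraoperative findings, for instance, the length of lesions did not match the stents".
- **Statistical analysis:** the primary and secondary endpoints use a modified ITT set, "which includes all subjects undergo randomization and subsequent interventions". The per-protocol set follows the treatment actually received. Noninferiority requires the ITT and per-protocol conclusions to agree.

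**The concern.** An eligibility test should be finished before the allocation is known, and it should be the same test in both arms. Criterion 4 can be settled only during the procedure, and its pre-dilation part uses a balloon whose size depends on the arm. The person who judges it knows the arm. A lesion found unsuitable at that stage has already been randomised, and the wording of the primary set gives a route by which it can leave the analysis.

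Stent switching adds to this. The plan gives length mismatch as an example, not as the only permitted reason, so the unblinded operator has wide discretion. The two devices come in different lengths (longest 58 mm for the CBE stent and 100 mm for the CSE stent, section on the CBE and CSE stents), so the pressure to switch need not be equal between arms.

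At stake is the comparability of the arms in the primary analysis of a small noninferiority trial. Selective losses can move the estimated difference either way. Switches analysed as randomised pull the difference towards zero, which helps a noninferiority claim when the CBE stent is truly worse.

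**Working it through.** **Order of events.** The point turns on what the word intervention means in the allocation section and in the definition of the modified ITT set. Two readings are possible.

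1. *Intervention means the whole endovascular procedure.* Disclosure comes before access, crossing and pre-dilation, so all of criterion 4 is judged with the arm known. A patient with a failed crossing has had an intervention and would stay in the modified ITT set, yet fails an inclusion criterion. The article does not say which prevails.
2. *Intervention means placing the stent.* Crossing may then precede disclosure. Pre-dilation cannot, because the balloon size depends on the arm. A lesion that fails at pre-dilation and is not stented has been randomised but has no subsequent intervention, so it falls outside the primary set.

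Under both readings, pre-dilation is judged after the arm is known.

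**Arm size used.** The plan states 53 lesions per group (Sample size calculation). With patency 82.2% and 89.1%, margin 10 points, one-sided 0.05 and 80% power:

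n = (1.645 + 0.842)² × (0.822×0.178 + 0.891×0.109) / (0.10 + 0.069)² = 52.7, so 53.

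That is the figure before dropout; 53/0.85 = 62.4, so 63 after it. This is a separate matter, and 53 is used below as stated.

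**Weight of one lesion.** 1/53 = 1.9 points of an arm. 5-10% of 53 is about 3-5 lesions.

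**Shift from one-sided exclusion.** Assumptions: a fraction f of one arm is dropped, and half of those lesions would have failed. The plan gives neither figure. Failure is taken as loss of 9-month primary patency, the only rate the plan supplies. The observed rate is (p − f×0.5)/(1 − f).

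- CSE arm, p = 17.8%: f = 5% gives (0.178 − 0.025)/0.95 = 16.1%, a shift of 1.7 points; f = 10% gives (0.178 − 0.05)/0.90 = 14.2%, a shift of 3.6 points. CSE looks better, so noninferiority of CBE is harder to show.
- CBE arm, p = 10.9%: f = 5% gives (0.109 − 0.025)/0.95 = 8.8%, a shift of 2.1 points; f = 10% gives (0.109 − 0.05)/0.90 = 6.6%, a shift of 4.3 points. CBE looks better, so noninferiority is easier to show.
- If the dropped lesions have the arm's average failure rate, the shift is zero.

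**Effect on false noninferiority.** Take the truth at the margin: CSE patency 82.2%, CBE 72.2%, n held at 53. The chance of declaring noninferiority is Φ((0.10 − d)/SE − z), where d is the observed difference and SE = √[(p₁(1−p₁) + p₂(1−p₂))/53]. The plan does not state the sidedness of its 0.05, so both cases are shown.

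- No exclusion or switch: 5% (one-sided 0.05) or 2.5% (one-sided 0.025).
- 5% of the CBE arm dropped, half of them failures: CBE patency 73.4%; 6.7% or 3.5%.
- 10% of the CBE arm dropped, half of them failures: CBE patency 74.7%; 9.1% or 4.9%.
- 10% switched in one arm, analysed as randomised, each taking the other device's average result: difference 0.10 × 0.9 = 9 points; 6.4% or 3.3%.
- 10% switched in both arms: difference 0.10 × 0.8 = 8 points; 8.2% or 4.4%.

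**The case against.** The strongest reply is that several harsher readings go beyond the text.

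- *A reader might infer that disclosure certainly comes before crossing.* This is the natural reading but not the only one: the nurse is in the operating room and the interventions being allocated are the stents. The flow figure and the schedule table are not available here and may fix the order. The objection stands for crossing. It does not reach pre-dilation.
- *A reader might infer that patients who fail criterion 4 are removed.* No sentence says so. Removal is inferred from the criterion together with the definition of the primary set, and a fuller document may state how these cases are handled. Switching, by contrast, is explicit.
- *A reader might infer that lesion length is unknown until after allocation.* The documents do not support this. Anatomic parameters are taken from the imaging archive (Data collection and management), and criterion 3 already refers to the TASC II class. The ruler reading during the procedure may only confirm what is known.
- *Criterion 4 asks for an appropriately sized balloon, which fits both arms.* True, and nothing shows that pre-dilation fails more often with one size than the other. The point is that failure can differ by arm, not that it does.
- *The requirement that ITT and per-protocol conclusions agree guards against dilution.* It does in part: dilution in the ITT set alone cannot deliver the claim. But the per-protocol set follows the treatment the surgeon chose after learning the arm, so it is itself open to selection.
- *A lesion never crossed receives no stent, so revascularisation on loss of patency is not naturally defined for it.* This is fair, and it is a reason to settle crossing before allocation.

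**Conclusion.** The point holds in a limited form. Criterion 4, the timing of disclosure and the arm-specific pre-dilation cannot all stand as written if eligibility is to be complete before allocation is known. At least pre-dilation, and on the natural reading crossing too, is judged by an unblinded operator, and open-ended switching adds a second route by which the arms can diverge.

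The size is uncertain. The 2-4 point shift rests on assumed figures of 5-10% of one arm lost and 50% failure among the lost lesions. It is modest against a 10-point margin but not negligible with 53 lesions per arm.

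A reader might conclude that the design pushes the trial towards noninferiority. The documents do not support that as a general statement. Exclusions favour CBE if they fall in the CBE arm and CSE if they fall in the CSE arm. Dilution by switching helps noninferiority only when CBE is truly worse, although that is the case the test has to guard against.

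**What to change.** Reconcile the eligibility, allocation and intervention sections so that eligibility is complete before the allocation is disclosed:

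1. Open the envelope after the wire has crossed and before any arm-specific step, once the surgeon has recorded that either stent could be used.
2. Take the arm-dependent pre-dilation condition out of eligibility. Which balloon sizing is right is not judged here.
3. Define the primary analysis set as every lesion whose envelope was opened, analysed as randomised, and state in advance how an opened but unstented lesion is counted.
4. Report exclusions and stent switches by arm, with the reason for each.

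The nurse and the envelopes are already in the operating room, so the cost is a short wait in theatre with both stent types at hand. Requiring that either stent be usable may narrow the population slightly. Enrolment began on 1 June 2020 and was due to end on 1 June 2022, and the article appeared on 12 May 2022. The timing change would therefore affect only later enrolments. The analysis-set definition and the reporting by arm can apply to every lesion in the trial.
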